#### Diagnosis

The diagnoses are based on the Structured Clinical Interview for Diagnostic and Statistical Manual of Mental Disorders (DSM-V) axis I disorders [40]. All interviewers engaged in diagnostics participate in supervised diagnostic evaluation meetings on a regular basis.

### Intervention

The exercise sessions will be conducted at the Buskerud and Vestfold University College and the computer gaming at a local high school in Tønsberg. Supervision of participants in the two groups is carried out by the same personnel employed in the outpatient clinics and dedicated to the project throughout the data collection period. The time spent with activities, as well as time spent with the intervention staff, is the same in both groups, and a specific time schedule is followed by the staff to ensure that each session in the exercise and comparison groups last 45 minutes. Participants in both groups are also accompanied by the project personnel during transportation, during the sessions of the intervention and during breaks.

The exercise sessions consist of supervised walking/running on a treadmill twice per week for 12 weeks. Each session will have the following structure; 8-minute warm-up, followed by 4x4 minute intervals with 85–95 % of maximum heart rate, with active pauses of 3 minutes walking/running at approximately 70 % of maximum heart rate. Heart rate will be measured and controlled continuously throughout the exercise session by research personnel with a heart rate monitor (RCX3 heart monitor from Polar (Polar Electro Oy, 90440 Kempele, Finland)) to ensure that the participants intervals and active pauses are performed with the desired intensity. The exercise session will end with a 5-minute cool-down period. The goal is to have the participants adhere to the protocol. However, we realize that some participants might have difficulties with this intensive program in the beginning of the intervention, and, thus, the protocol will be individualized and progressive both in terms of the number of intervals and the intensity. This high-intensity exercise performed as 4x4 minute intervals has previously been shown to be feasible, safe and effective for individuals with schizophrenia [41] and other clinical populations [21, 22, 26, 27, 38].

Participants in the comparison group take part in sessions performing computer-simulated sports activities (Nintendo Wii Sports (Nintendo, Frankfurt am Main, Germany) tennis, baseball, golf, bowling). Physiological responses (i.e. oxygen consumption, cardiac output, metabolic rate) of Nintendo Wii tennis (and baseball) has shown to be lower than brisk treadmill walking when tested in bouts of 10 minutes [42]. Through comparing neurocognitive and symptom scores in a group that is physically active with the performance of a group that simulates such activity, we expect to be able to extract the net effect of high-intensity exercise. Changes in simulated sports skills are monitored and continuous feedback is given to the participants by supervising personnel.

### Treatment as usual

All participants are registered outpatients at the psychiatric rehabilitation clinics in Tønsberg (NVDPS) or Larvik (SVDPS) in Vestfold County and receive individual treatment during project participation. The treatment is based on appointments at the clinic and/or home visits, and may include pharmacological treatment, individual psychotherapy, family interventions, and general psychosocial support through extensive collaboration with primary care health services. Episodes of illness exacerbation may require acute or planned admittance to local or county-level inpatient units, usually of short-term duration, while remaining registered at the outpatient clinic and continuing project participation.

### Feasibility study

A feasibility study was conducted from November 2013 through January 2014. Participants were outpatients at NVDPS Tønsberg and had present or previous psychotic symptoms. Apart from minor alterations, the same study protocol was followed as in the main trial. The intervention period was, however, considerably shorter, ranging from 3 to 6 weeks. Group assignment was not randomized in the feasibility study, and the raters were not blinded. Ten patients, 6 men and 4 women, aged 22–64 years (mean age 41) completed the study; 6 in the EG and 4 in the comparison group. The main purpose of the feasibility study was to gain experience with practical aspects of the protocol, evaluating its viability through particular focus on feedback from participants.

### Assessments

Participants will be assessed at three time points. The content of the assessments are outlined in Table 2. The first assessment occurs at baseline (T_0_) prior to randomization, because information from the baseline assessment is needed for validation of the inclusion and exclusion criteria and required for the stratification. The second assessment takes place immediately after completion of the intervention (T_1_). Longer-term outcomes or possible delayed effects not evident already at intervention cessation are tested in the third assessment 4 months post-treatment (T_2_).

**Table 2 Tab2:** Assessments in the Effects of PHysical Activity in PSychosis (EPHAPS) trial

	Enrollment	Baseline	Randomization	Follow-up 1	Follow-up 2
TIME POINT		T_0_	0	T_1 12 weeks_	T_2 28 weeks_
ENROLLMENT					
Eligibility screen	X				
Informed consent	X				
Allocation			X		
INTERVENTIONS					
Exercise Group (EG)			>---------------<		
Computer Gaming Skills Group (CSG)			>---------------<		
ASSESSMENTS					
General assessments					
Sociodemographic data		X			
Changes in employment status				X	X
Information on tobacco, dietary habits and current level of physical activity		X			
Changes in use of tobacco, dietary habits, medication				X	X
Somatic health					
Physical examination: height; electrocardiography (ECG); medication record		X			
Weight, waist circumference, blood pressure		X		X	X
Changes in medication				X	X
Body composition assessment (bioelectrical impedance analysis/Tanita-weight)		X		X	X
Blood analyses: glucose, HbA1c, C-peptide, lipids (total cholesterol, HDL, LDL, TGA), homocystein, prolactin, T4, TSH, BDNF		X		X	X
Spirometry (pulmonary function test)		X		X	X
Cardiorespiratory fitness, physical activity and sleeping habits					
Maximal oxygen consumption		X		X	X
ActiGraph accelerometers (4 days)		X		X	X
Attitudes towards physical activity (PA)		X			
Change in attitudes towards PA (two selected items from Attitudes towards PA)				X	X
International Physical Activity Questionnaire (IPAQ)		X		X	X
Assessment of insomnia: Insomnia Severity Index (ISI)		X		X	X
Psychoactive substance use					
Selected parts of European Addiction Severity Index (EuropASI)		X		X	X
SCID section E		X			
Alcohol and Drug Use Disorder Identification Test (AUDIT and DUDIT)		X			
Alcohol and Drug Use Scale (AUS and DUS)		X		X	X
Fagerström test for Nicotine Dependence (FTND)		X		X	X
Saliva samples for assessing recent intake of tobacco, alcohol, illegal drugs and legal medication with abuse potential		X		X	X
Neurocognitive tests					
General Ability Index (GAI, Wechsler Adult Intelligence Scale-version 4)		X		X	X
The Emotional Biological Motion Test		X		X	X
Matrics Consensus Cognitive Battery (MCCB)		X		X	X
Diagnostics/symptoms/wellbeing					
The Structural Clinical Interview DSM-IV for axis I disorders (SCID-I)		X			
The Positive and Negative Syndrome Scale (PANSS)		X		X	X
The Psychotic Symptom Rating Scale (PSYRATS)		X		X	X
The revised Beliefs About Voices Questionnaire (BAVQ)		X			
Positive and Negative Affects Schedule (PANAS)		X		X	X
Depression: Calgary Depression Scale for Schizophrenia (CDSS)		X		X	X
WHO-5 Well-Being Index		X		X	X
Self-esteem (Ad Morrison)					
Clinical Global Impression Scale (CGI)		X		X	X
Psychosocial functioning					
Global Assessment of Functioning (GAFs and GAFf)		X		X	X
Quality of Life (Strauss Carpenter Level of Function (SCLOF))		X		X	X
Insight/adherence/apathy					
Insight of illness: Birchwood Insight Scale; cognitive insight: Beck Cognitive Insight Scale		X		X	X
Adherence to treatment: The Believes about Medicines Questionnaire (BMQ)		X		X	X
Apathy: Apathy Evaluation Scale (AES)		X		X	X

The table depicts specific time points in the trial for enrolment, intervention (groups and duration), and the assessments

*BDNF* brain-derived neurotropic factor, *HbA1c* glycosylated hemoglobin, *HDL* high-density lipoprotein, *LDL* low-density lipoprotein, *T4* thyroxine, *TGA* triglycerides, *TSH* thyroid stimulating hormone

Neurocognitive function is the primary outcome in the trial. Secondary outcome measures are positive and negative symptoms, wellbeing, as well as smoking habits, and somatic health parameters such as pulmonary function, body mass composition (e.g. body fat, bone mass), blood pressure, abdominal circumference, serum lipids, blood glucose. Brain-derived neurotrophic factor (BDNF), an important biomarker for neuroplasticity that seems to be upregulated after physical activity in schizophrenia [23] is also a secondary outcome measure. The changes in symptom level, wellbeing, neurocognitive scores and physiological (e.g. maximum oxygen uptake) and metabolic indices are assessed from T_0_ to T_1_ and from T_1_ to T_2_.

#### Symptoms, affect and wellbeing

Psychosis symptoms are assessed using the Positive and Negative Syndrome Scale for Schizophrenia [43]. Characteristics of delusions and hallucinations are specified using The Psychotic Symptom Rating Scale (PSYRATS, [44]), also targeting the distress dimension of these symptoms at baseline and changes therein between T_0_ and T_1_ and between T_1_ and T_2_ respectively. For endorsement of patients’ beliefs, emotions and behaviour related to auditory hallucinations, the revised Beliefs About Voices Questionnaire (BAVQ-R, [45, 46]) is applied. Participants’ depressive thinking is assessed by the Calgary Depression Scale for Schizophrenia (CDSS) [47, 48].

The degree of positive feelings towards oneself, life and future is not necessarily dependent on the occurrence and intensity of symptoms, even in the realm of severe, psychotic disorders. The dominating emotional tone of the present is assessed by The Positive and Negative Affect Schedule (PANAS), comprised of two statistically largely independent scales [49, 50]. The self-report is administered to all patients in both intervention groups at T_0_, T_1_ and T_2_, and, for measuring possible immediate effects, mid-intervention, after completing scheduled activity on a particular day, in addition to the PANAS assessment immediately after neurocognitive testing at T_2_. Self-esteem is assessed using a self-rating scale (Ad Morrison). General symptoms are appraised using the Clinical Global Impression Scale (CGI, [51]). Wellbeing is assessed using the 5-item self-report World Health Organization-5 (WHO-5) Well-Being Index [52]. The questionnaire has previously been used to monitor treatment in affective disorders [53].

#### Neurocognitive tests

Neurocognition is assessed with the Matrics Consensus Cognitive Battery (MCCB), which is developed particularly for assessment of treatment changes in schizophrenia. It assesses cognitive function in seven domains, including those most probable to increase as a function of increased cardiorespiratory fitness (executive functions, attention and memory) and offers parallel forms for repetitive testing. MCCB has been used in previous studies in Norway and the Norwegian Version has retained the original psychometric properties [54] with the possible exception of the test intended to measure social cognition. This subtest will be replaced by The Emotional Biological Motion Test [55], which is an experimental test newly developed by leading research groups in this field. At baseline participants will be examined with 6 subtests from the Wechsler Adult Intelligence Test-version 4, resulting in a General Ability Index-score equivalent to a full scale IQ.

#### Sociodemography

Basic sociodemographic data is collected, including sex, age, education, marital status, employment, living conditions, etc.

#### Lifestyle

Basic lifestyle parameters are assessed, including dietary habits, daily activity level, and daily use of stimulants containing caffeine and nicotine. Psychoactive substance use is thoroughly covered; see below.

#### Somatic health

A physical examination with medication record is undertaken in the trial. All participants are examined with electrocardiography (ECG). General health parameters such as weight, waist circumference and blood pressure, as well as pulmonary function and body composition are assessed. Blood samples, which encompass standard blood tests in addition to BDNF, will be collected from participants following overnight fasting at the three assessment points. For analysis of BDNF venous blood samples are collected in tubes containing ethylenediaminetetraacetic acid (EDTA). After centrifugation at 2500 g for 20 minutes, platelet-poor plasma will be isolated, aliquoted and stored at −80 °C. At the end of data collection, all samples will be analyzed for BDNF concentrations using enzyme immunoassay at the Research Institute for Internal Medicine, Rikshospitalet, Oslo, Norway.

#### Cardiorespiratory fitness, physical activity and sleeping habits

Maximal oxygen uptake (VO_2max_) is measured during a maximum exercise test on a treadmill using a modified Balke protocol [56]. Gas exchange is sampled continuously into a mixing chamber every 30 s by having the participants breathe into a Hans Rudolph 2-way breathing valve (2700 series, Hans Rudolph Inc., Kansas City, MO, USA) connected to a Jaeger Oxycon Pro gas analyzer (Erich Jaeger GmbH, Hoechberg, Germany), which measures the oxygen and carbon dioxide content.

Physical activity level is measured both objectively (ActiGraph accelerometer GT3X+ (ActiGraph, Pensacola, FL, USA) worn on the hip for 4 consecutive days; 2 weekdays and 2 days of the weekend) and subjectively using the International Physical Activity Questionnaire (IPAQ, short form [57, 58]). In addition, potential psychosocial mediators for change in physical activity and attitudes towards physical activity will be measured by previously developed and validated scales: social support for physical activity [59, 60], self-efficacy and outcome expectancies and attitudes [61, 62]. Sleeping habits are assessed using the ActiGraph data as well as the brief Insomnia Severity Index (ISI, [63]).

#### Psychoactive substance use

At baseline, a diagnostic assessment of psychoactive substance use is performed with the SCID section E (including alcohol, illegal drugs and legal drugs with abuse potential), and the severity of such use is additionally measured with the Alcohol and Drug Use Disorder Identification Tests (AUDIT [64] and DUDIT [65]). Assessments at 3 time points (T_0_/T_1_/T_2_) will include selected parts of the European Addiction Severity Index (EuropASI) [66], Alcohol [67] and Drug Use Scales [68] (AUS and DUS respectively), Fagerström test for Nicotine Dependence [69] and saliva samples for assessing recent intake of tobacco, alcohol, illegal drugs and legal medication with abuse potential. The toxicological analyses will be performed at Division of Forensic Toxicology and Drug Abuse Research, Norwegian Institute of Public Health.

#### Psychosocial functioning, adherence and insight

Strauss Carpenter Level of Functioning Scale (SCLOF) is utilized for the endorsement of patients’ social and work functioning. Global Assessment of Functioning (GAF, [70]) is divided into two scales measuring symptoms (GAFs) and function (GAFf) to improve psychometric properties [71]. Insight of illness (Birchwood Insight Scale, IS, [72]), cognitive insight (Beck Cognitive Insight Scale, BCIS, [73]) and apathy (Apathy Evaluation Scale, AES, [74]) are assessed using self-rating scales.

### Protocol deviations

When absent from scheduled exercise or computer gaming, the participant will be contacted and offered to participate on a following day the same week. Participants who fail to complete at least 60 % of the total number of intervention sessions or have not participated for more than 2 successive weeks are considered protocol violators. Participants who are unable to meet for the VO_2max_ test within 10 days following the last training session will also be considered protocol violators. However, they will be allowed to stay in the study and will be tested as soon as possible, as well as invited to take part in T_2_. Statistical analyses will be performed both based on the principle of “intention-to-treat” including everyone regardless of protocol violations, but “per protocol” analyses will also be executed, comparing only those who completed the two treatment conditions according to the protocol.

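### A late VO2max test makes even a fully attending participant a protocol violator, and so appears to remove that participant from the per-protocol comparison of cognition, symptoms and wellbeing

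*Protocol article*

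**What the plan says.** The Protocol deviations section of the protocol article gives three routes to violator status. Two concern treatment received: participants who "fail to complete at least 60 % of the total number of intervention sessions", and those who "have not participated for more than 2 successive weeks are considered protocol violators". The third concerns the date of one assessment: those unable to meet for the VO2max "test within 10 days following the last training session will also be considered protocol violators". For people in this third group, the section adds that "they will be allowed to stay in the study and will be tested as soon as possible", and they are invited to T2.

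The same section then names two analyses. Intention-to-treat is described as "including everyone regardless of protocol violations". Per-protocol is described as "comparing only those who completed the two treatment conditions according to the protocol". No separate per-protocol set is given for any outcome.

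The Assessments section states: "Neurocognitive function is the primary outcome in the trial". It places the T1 assessment directly after the intervention ends and gives no number of days for the cognitive or symptom measures.

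**The concern.** A per-protocol set is meant to describe people who received the treatment as planned. The two session rules do that. The VO2max rule does not: it records when a fitness test took place. Applied to the cognitive comparison, it can drop people who had the full intervention and a valid cognitive assessment.

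Two things are at stake. Precision falls, because adherent participants are lost. There may also be extra selection, because turning up on time for a maximal treadmill test is behaviour after randomisation. It could depend on motivation or symptoms, and it could differ between an arm that trained on a treadmill and one that played computer games.

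The per-protocol results may well attract attention. The Background describes an earlier exercise trial whose effects were significant per protocol but not by intention to treat.

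**Working it through.** **1. What the rules do to individual participants**

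The Intervention section sets the exercise arm at "supervised walking/running on a treadmill twice per week for 12 weeks", so 2 × 12 = 24 sessions. It says that activity time is the same in both groups. The attendance threshold is 0.60 × 24 = 14.4, so 15 sessions are enough.

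| Participant | Sessions | Gap over 2 weeks | VO2max test after last session | Status |
|---|---|---|---|---|
| A | 24/24 | no | day 11 | violator |
| B | 15/24 | no | day 10 | not a violator |

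A received everything planned and B missed 24 − 15 = 9 sessions, yet only A is a violator. This result needs no assumption.

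**2. Whether violators leave the per-protocol set**

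The article does not say so in terms. It contrasts an analysis that ignores violations with one restricted to completion according to the protocol, directly after defining violators. Exclusion is the natural reading. If it is not intended, the VO2max rule has no stated role in the analysis and the text still needs clarifying.

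**3. Loss of precision (illustration)**

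Inputs from Sample size calculations: 55 per group, difference 0.50 SD, alpha 0.05. Two-sided testing is my assumption, since the article does not state it. I also assume that late tests are the only exclusions. The late-test rate is not in the documents and is varied.

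Power ≈ Φ(0.50 × √(n/2) − 1.96)

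| Assumed late in each arm | n per arm | Power |
|---|---|---|
| 0% | 55 | 0.75 |
| 5% | 52.25 | 0.72 |
| 10% | 49.5 | 0.70 |
| 20% | 44 | 0.65 |

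The first row is below the planned 0.80 for a reason unrelated to this rule. Only the drop from row to row belongs to it: 0.02 to 0.10.

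**4. Possible selection (illustration)**

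Let D be the amount, in SD, by which the cognitive change of those excluded falls short of those retained. Let p be the excluded share in each arm. Each retained mean is raised by p × D, so the shift in the EG − CSG difference is D × (p_EG − p_CSG).

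With assumed p_EG = 0.10 and p_CSG = 0.30:
- D = 0.3 gives 0.3 × (−0.20) = −0.06 SD.
- D = 0.5 gives 0.5 × (−0.20) = −0.10 SD.

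These are 12% and 20% of the 0.50 SD target. The sign is negative, so the difference shrinks. With the two rates exchanged, the shift would be +0.06 to +0.10 SD. With equal rates and equal D in both arms, it is zero.

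**The case against.** **The trial's primary data are not lost.** A reader might infer that the rule discards valid data on the primary outcome. The documents do not support that: late-tested participants stay in the study and are in the intention-to-treat analysis. Only the per-protocol analyses, which the article adds alongside it, are touched. This stands in full.

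**The exclusion is inferred.** Someone with 24/24 sessions has arguably completed the treatment condition, and the full protocol or analysis plan may set outcome-specific populations. This stands as a caution, but the rule as printed carries no such limit.

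**The window has a purpose, and the dates may be related.** Fitness is the proposed mediator, and the Statistical analysis section plans to correlate outcome changes with fitness changes, which calls for VO2max to be measured soon after training. VO2max and the cognitive battery also share the T1 assessment, so a late treadmill test may go with a late cognitive test. It would therefore be too strong to say that the VO2max date carries no information about the cognitive test date. Even so, this argues for a window on the cognitive test itself.

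**Differential selection is unproven.** A reader might infer that the rule selects on a factor tied to both arm and outcome. The documents report no late-test rate, overall or by arm. Both arms have the same staff, accompanied transport and, according to the Discussion, equally comprehensive support. This stands: dependence on arm is possible, not shown.

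**Session rules select too.** Attending at least 60% of sessions is also behaviour after randomisation. True: the fix removes one selection step and leaves that one in place.

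**Conclusion.** The point holds in a limited form. As printed, violator status depends in part on the date of a fitness test and is not restricted to fitness outcomes. On the natural reading, session-adherent participants are left out of the per-protocol comparison of cognition, symptoms and wellbeing, for a reason that does not measure treatment received.

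The consequence is some loss of precision and a possible additional post-randomisation selection in supporting analyses. Neither can be sized from the documents. The late-test rates, any difference between arms and the deficit in those excluded are all assumptions. Nor do the documents support a reading that the rule favours exercise: if the comparison arm lost more of its poor performers, the EG − CSG difference would shrink. The change is worth making because it is cheap and the rule works against the purpose of the set.

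**What to change.** Define per-protocol status for cognitive, symptom and wellbeing outcomes by the two session rules alone: at least 60% of sessions, and no gap of more than 2 successive weeks. Apply the 10-day VO2max window only to analyses of VO2max or fitness change, including their correlation with change in other outcomes. If the timing of T1 matters for cognition, set a window on the date of the cognitive test.

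The cost is one sentence. The per-protocol set will then differ by outcome, which needs a footnote wherever per-protocol results are reported.
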